Secondary aims of this study are to investigate a) whether the effectiveness of the intervention is related to factors like age, diagnosis, or muscle strength and clinical SVMC measures at baseline; b) the time to response, i.e., amount of training needed until a meaningful improvement in SVMC can be expected; c) the effect of the intervention on clinical measures of SVMC, muscle strength, cortical excitability, motor control of the inhibited movement, and functional independence; d) the association of changes in SVMC with changes in muscle strength or cortical excitability; and e) whether potential changes in SVMC, muscle strength, and functional independence are maintained three months after the intervention.

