### Study design

We will use a randomized, non-concurrent, multiple baseline design across participants to investigate the efficacy of our game-based intervention to improve SVMC. The study will consist of a baseline phase of random length, i.e., 5 to 8 short assessment sessions distributed over 5 to 10 weekdays. The assessment sessions will include the measurement of the primary outcome (a short game-based SVMC assessment) and dynamometry of the target muscle group. During the intervention phase, participants will receive 10 treatment sessions of 40 min of our game-based SVMC training during 10 to 13 weekdays, while the short assessment will be continued (Fig. 1). Participants will train selective control of one individually determined target movement or muscle group, while trying to reduce the occurrence of involuntary movements or muscle activations around another predefined joint. Further assessments (see outcome measures) will be conducted at the beginning of the baseline phase, at the transition from the baseline to the intervention phase, at the end of the intervention phase, and at a follow-up 12 weeks after completion of the intervention.

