### Sample size calculation

We approximate the number of participants needed with calculations based on a general linear model and later correct for the fact that measurements from one participant are not independent observations (clustering). In a general linear model, 78.4 observations are sufficient to detect a medium to large effect (r = 0.4, R^2^ = 0.16) [35] with a power of 90%, α = 0.05 and 3 degrees of freedom for the numerator (two fixed effects and one random effect), calculated with the pwr.f2.test function of the R package ‘pwr’ [36].

The correction, also called the design effect, accounts for the degree of variance inflation that attributes to clustering (several measurements from one participant). The design effect equals 1 + (*m* − 1) ∗ *ρ*, where m is the number of data points per cluster (i.e., participant) and ρ is the intraclass correlation within clusters [37]. We estimate ρ = 0.18 for the percentage score combining the accuracy and involuntary movement outcome based on unpublished data from our pilot study with six participants. In this trial, the mini-assessment was conducted three times before the first training and once before and after the following 4 training sessions. According to the formula, the design effect thus equals 3.80, assuming that m = 16.5 data points will be recorded for a person on average (i.e., expected value for randomly between 5 and 8 assessments in the baseline phase and 10 during the intervention).

Multiplying 78.4 with the design effect yields the total number of observations needed, which is then divided by 16.5 observations per person. Allowing a dropout rate of 10%, we will need 20 participants.

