To analyze the association of changes in SVMC and muscle strength, we will correlate the regression coefficients for the interaction of the session and treatment phase from the strength and the SVMC model of each individual participant. For TMS outcomes, we will further correlate pre- to post-intervention differences with changes in SVMC measures. Follow-up data will be analyzed by paired comparisons (t-test or robust alternative) between post-intervention and follow-up assessments (to test whether the level is maintained) and between the measurement directly before the intervention and at follow-up (to test whether the level is still higher than before starting the intervention).

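### The paired difference test planned for the 12-week follow-up cannot show that the post-intervention level is maintained, and with about 18 children a non-significant result says little

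*Protocol article*

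**What the plan says.** The last of the secondary aims in the Background section asks "whether potential changes in SVMC, muscle strength, and functional independence are maintained three months after the intervention". The Study design section places the final assessment "at a follow-up 12 weeks after completion of the intervention".

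The analysis is fixed at the end of the Secondary research aims part of the Statistics section: "Follow-up data will be analyzed by paired comparisons (t-test or robust alternative"). Two comparisons are named, each with its purpose. The first is "between post-intervention and follow-up assessments (to test whether the level is maintained"). The second sets the measurement just before the intervention against follow-up, "to test whether the level is still higher than before starting the intervention". The article attaches no margin, equivalence rule or confidence-interval criterion to the first comparison.

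The number of children comes from the Sample size calculation section, which sizes the primary mixed model: "Allowing a dropout rate of 10%, we will need 20 participants".

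**The concern.** The first follow-up comparison is given a purpose that it cannot serve. A paired t-test, or a robust counterpart, takes no difference as its null hypothesis. Rejecting it shows that the level changed. Not rejecting it shows only that the data did not rule out no change, and they may equally not rule out a material loss. Yet non-rejection is the only outcome of this test that could be taken to mean the level was maintained.

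The incentive also runs the wrong way. The fewer children who return at 12 weeks, and the noisier their scores, the more likely this comparison is to come out non-significant. At stake is the statement on durability that the report will make under aim (e).

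The point is not that a margin is missing, since an analysis plan could supply one. The article names both the test and its purpose, and the two do not match.

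**Working it through.** **Inputs.** Enrolment of 20 and dropout of 10% come from the Sample size calculation section. That section also gives the significance level, "with a power of 90%, α = 0.05 and 3 degrees of freedom for the numerator", but for the primary model only. No level or sidedness is stated for the follow-up tests, so two-sided 5% is assumed. The SD of the within-child difference between post-intervention and follow-up (SD_d) is not given. Results are therefore in units of SD_d first, then over a range. Loss means worsening, whichever way a scale runs.

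**Step 1: the plan's own figure.** The noncentral F calculation with 3 numerator degrees of freedom, f² = 0.16/0.84 = 0.1905, α = 0.05 and 90% power gives 78.43 observations (stated: 78.4). The design effect is 1 + (16.5 − 1) × 0.18 = 3.79 (stated: 3.80). Then 78.4 × 3.80 / 16.5 = 18.06 children, and 18.06 / 0.9 = 20.06. The stated 20 is reproduced. With 10% dropout, 20 × 0.9 = 18 pairs, provided that the allowance holds to 12 weeks.

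**Step 2: precision with 18 pairs.** The half-width of the 95% CI is t(0.975; 17) / √18 × SD_d = 2.110 / 4.243 × SD_d = 0.50 SD_d. An observed loss just short of significance (0.50 SD_d) therefore has a CI that reaches about 0.99 SD_d.

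**Step 3: chance of a non-significant result.** Power comes from the noncentral t distribution with 17 degrees of freedom and noncentrality d√18, where d is the true loss divided by SD_d.

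| True loss (SD_d) | Non-significant, n = 18 | Non-significant, n = 20 |
|---|---|---|
| 0.3 | 78% | 75% |
| 0.5 | 48% | 44% |
| 0.8 | 11% | 8% |

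The loss detectable with 80% power is 0.70 SD_d at n = 18, 0.66 at n = 20 and 0.78 at n = 15.

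**Step 4: the percentage scale of the mini-assessment.** A 10-point loss is used for illustration because the plan's response criterion is a 10% improvement. The SDs are assumptions. The value of 14 is √2 × 10, which is what measurement error alone would give if the standard error of measurement were 10 points.

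| Assumed SD_d (points) | 10-point loss non-significant, n = 18 | Upper CI limit for loss when just non-significant (points) |
|---|---|---|
| 10 | 2% | 10 |
| 14 | 19% | 14 |
| 20 | 48% | 20 |
| 30 | 73% | 30 |

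**Step 5: what a properly directed test could do.** Test the paired change against a margin at one-sided 2.5%, with no true loss. Power with 18 children is 22% for a margin of 0.3 SD_d, 52% for 0.5, 80% for 0.7 and 98% for 1.0. For 80% power, margins of 0.3, 0.5 and 0.7 SD_d need 90, 34 and 19 children.

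**The case against.** The strongest reply is that the plan has two follow-up comparisons. The one between pre-intervention and follow-up is correctly directed: a favourable answer needs a rejection, so low power and attrition count against it. A reader might infer that aim (e) as a whole is answered favourably through lack of power. The documents do not support that, because it is true of only one of the two tests. What remains is that the second test asks whether any gain is left. A group could lose most of its gain and still pass it. If both tests were non-significant, the results could be taken to say both that the level was maintained and that it was not shown to exceed the starting level. The article gives no rule for that case.

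A second reply is that the article never says a non-significant result will be read as maintenance. That is correct, and the reading is an inference. It rests on the stated purpose of the test, which no other outcome of the test could meet.

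A third reply is that a large loss has not been shown to go unnoticed. This also stands in part. A loss of 0.8 SD_d is missed only 11% of the time, and with an SD_d of 10 points a 10-point loss would almost always be found. The problem is mild at that SD and serious at 20 points or more, and the document does not say which applies.

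**Conclusion.** The point holds for the first follow-up comparison: as described, it can show loss but cannot show maintenance. With 18 pairs at a two-sided 5% level, a true loss of 0.5 SD of the paired difference goes undetected about half the time (48%), and only losses of about 0.70 SD or more are found with 80% power. On the percentage scale, the chance of missing a 10-point loss runs from 2% to 73% over assumed SDs of 10 to 30 points. These figures assume that the 10% dropout allowance holds to 12 weeks; greater loss to follow-up makes them worse.

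A reader might also infer that the plan already contains a margin, in the 10% change that it equates with about one standard error of measurement. It does not. That figure is the response threshold for the Kaplan-Meier analysis. As a margin, it would let a gain no larger than the threshold vanish without the loss exceeding the margin. The article gives no standard error of measurement for muscle strength, the WeeFIM or the individual clinical scales.

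The aim is secondary, and the primary conclusion is unaffected.

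**What to change.** For each follow-up outcome, report the mean change from post-intervention to follow-up with its 95% CI. Use the paired test only to show loss, and do not conclude maintenance from a non-significant result.

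If a maintenance claim is wanted, allow it only when the CI excludes a loss beyond a margin set in advance for that outcome. The margin must be smaller than the gain it is meant to preserve; a stated fraction of the pre-to-post gain is one example. In that case the gain is estimated from the same children, so the interval should be for a within-child contrast of the three measurements. The 10% response threshold should not be taken over as the margin without justification. Where the CI does not exclude the margin, report the result as inconclusive and rest the conclusion on the retained benefit shown by the pre-intervention versus follow-up comparison.

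The cost is a sentence or two and a margin for each outcome, with no extra assessments or children. The downside is that maintenance becomes harder to claim: with 18 children and no true loss, 80% power needs a margin of about 0.7 SD of the paired difference, so an inconclusive result is likely for tighter margins.

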## Discussion

This protocol paper describes the design of a randomized multiple baseline single-case design study to investigate the effectiveness of a novel game-based intervention to improve SVMC in children with upper motor neuron lesions.

Single case designs have been used in educational research for many years and are emerging in research concerning children with CP [39]. Repeated assessment of the outcome throughout distinct phases of a study is a key element of single-case experimental designs, as well as the concept that participants act as their own control [40–42]. These designs emphasize the individual cases and aim to describe and understand the variability between participants [43]. Group-design studies, like randomized controlled trials that are still considered the gold standard for evaluating treatment effects, are, for example, less suitable for small and heterogeneous samples [44]. For this reason, Romeiser-Logan et al. [45] argue that such research designs could be particularly suitable for pediatric rehabilitation. Using a single-case design also helps to handle the individualization of our intervention in terms of selecting the trained movement and the system to control the game. The application of a reversal design with withdrawal phases would not be suitable for this setting where carry-over effects are expected yet even aimed for [42]. Although increasing the length of the phases would be desirable (i.e., a higher number of data points, more treatment sessions), it has to be balanced against the length of the children’s stay at the clinic.

A limitation of the current study design is that it only investigates the effect of additionally providing our game-based SVMC training to regular rehabilitation but does not allow to compare the intervention to an equally dosed alternative treatment. However, this design was chosen because it will be the first time an SVMC training that targets both accurate movement control and a reduction of involuntary movements is investigated, and thus, this study can provide a first proof of principle. Moreover, the game-based SVMC intervention will only make up a small part of the therapy program the participant will receive during the study period. The intensive rehabilitation program running in the background of the study could affect the treatment effects. We might only see small differences between the baseline and the intervention phase because the regular rehabilitation program is included in both phases. However, we assume we will be able to see treatment effects because we focus very specifically on SVMC, and improving SVMC is rarely a therapeutic goal in other therapies [46]. Furthermore, we provide the intervention with a high frequency, i.e., the treatment sessions will be distributed over a short period. Apart from the frequency, the total dosage is comparable to the protocols of the few studies that aimed at improving aspects of SVMC so far, which applied training intensities between 4 and 9 h of treatment over 5 or 6 weeks [14, 15, 47, 48]. We account for the effects of the concomitant therapies as well as for spontaneous recovery in patients with subacute acquired brain injuries by comparing the trend of changes between the baseline and intervention phase or the changes relative to the length of the phases. Besides analyses on the group level, we will also look at each participant individually to address the heterogeneity of the study population.

This study will also serve to assess the responsiveness and determine the clinically meaningful change of two previously developed SVMC assessments [25, 26, 49]. These investigations were not included in the assessments’ preliminary psychometric testing due to the lack of an intervention specifically aiming to improve SVMC. The sEMG based similarity index recorded during the SCALE or SCUES and the assessgame will be conducted additionally before and after the intervention phase. We will assess meaningful change in SVMC using a global rating scale. The participant’s physical or occupational therapist (for lower or upper extremity target joints, respectively) will rate how SVMC of the participant has changed throughout the intervention on a five-point Likert scale: ‘much better’, ‘somewhat better’, ‘unchanged’, “somewhat worse’, ‘much worse’. We will also ask the participants themselves whether they have the impression, they can move their target joint more selectively. If therapists and particularly the participants would consider changes meaningful, this study would provide first evidence of efficacy and relevance of this game-based intervention to improve impairments in SVMC in children and adolescents with an upper motor lesion.

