Although the importance of selective motor control has been recognized in several cross-sectional studies, only a few interventions have specifically aimed to improve it [13]. For example, a robot-assisted ankle movement training implemented into a computer game was used to train graded ankle dorsi- and plantarflexion [14]. In another study, selective muscle activation was trained with a commercial video game controlled by surface electromyography signals to reinforce desired muscle activity and reduce co-contraction of the agonist-antagonist muscle pair [15]. Although both interventions could show promising results in preliminary studies so far, these training approaches can address only one specific aspect of SVMC (i.e., improving joint movement control or reducing agonist-antagonist co-contraction).

To fill this gap, we have recently developed an intervention specifically targeting the improvement of SVMC that intends to cover all features of reduced selective control. It consists of a game played in a virtual environment coupled to a technology-assisted interface to track joint movements. This allows to train accurate joint movement control, while it simultaneously provides immediate feedback about the occurrence of involuntary movements (via an alarm sound). Advantages of using interactive computer play technology are that playful environments can enhance motivation to enable large numbers of repetitions and the possibility to improve movement performance based on augmented feedback. Both are important aspects of motor learning during rehabilitation [16]. In a small pilot trial, five children with impaired SVMC completed five training sessions (lasting 45 min each) with the game-based intervention to enhance SVMC. It proved to be feasible and motivated participants to practice, but effects on SVMC were not examined [17]. Therefore, the primary aim of this study is to investigate the effectiveness of this game-based intervention in improving SVMC in children and youth with upper motor neuron lesions in a multiple baseline single-case design. Our hypothesis is that ten sessions of game-based training of SVMC concomitant to intensive rehabilitation improve SVMC more than standard rehabilitation alone.

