For the second approach to controlling the SVMC game, surface electromyographic (sEMG) signals of the target and involuntarily activated muscle groups are recorded using a varioport device (Becker Meditec, Karlsruhe, Germany) at a sampling frequency of 1000 Hz. Electrodes (Kendall H124SG) will be placed on the muscle belly of the two involved muscles and a reference electrode on a bony process. The sEMG signals are transferred via Bluetooth to the game computer, where they are filtered (exponential smoothing with a smoothing factor of 0.003 followed by taking a moving average with window size 10 frames). Increasing and lowering the activation of the target muscle causes the avatar to move upwards or downwards, respectively. Activity in the muscle that should remain inactive triggers the feedback signal. The target joint will be fixed in standardized positions (see Additional file 1) with Velcro straps and a customized board with loops screwed on it to enable isometric muscle activation. Isometric training was chosen since not restraining movement caused pain after only a short playing time in the pilot trial because the joint was mostly held in a position at the end of the ROM. To calibrate the system, we will record a 4 s baseline when participants relax and two maximal voluntary contractions (MVC). A baseline-corrected activity level of 20% MVC is required to reach the top position in the game, and the lowest position corresponds to 2% MVC (i.e., 10% of played range). If the control is too sensitive (i.e., due to a low MVC level resulting in a small signal range), the upper limit will be increased to maximize the range while keeping the effort reasonable.

Movements that can be trained comprise shoulder abduction, elbow flexion, wrist extension, finger flexion, knee extension, and ankle dorsiflexion. Participants will train selective control of one individual target movement while trying to reduce movements in one other joint. This combination will be selected according to the participants’ individual goals and in consultation with their therapist. Based on experience from the pilot trial [17], more proximal target joint movements (shoulder, elbow, and knee joint) will be trained with the ArmeoSenso unless in combination with a reduction of mirror movements (which the ArmeoSenso is unable to track). Movement at distal joints will be trained with the sEMG based system.

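### Global ratings of change include no rating of the rehabilitation-only phase, so they cannot carry the efficacy statement that the Discussion attaches to them

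*Protocol article*

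**What the plan says.** The final paragraph of the Discussion introduces the rating: "We will assess meaningful change in SVMC using a global rating scale". The rater is the physical therapist for lower-limb targets and the occupational therapist for upper-limb targets, who "will rate how SVMC of the participant has changed throughout the intervention on a five-point Likert scale". For the children it adds: "We will also ask the participants themselves whether they have the impression, they can move their target joint more selectively". That item states no reference period.

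The same paragraph gives the rating's main purpose, which is to help establish responsiveness and meaningful change for two existing SVMC assessments. It then closes with a conclusion about the treatment: "If therapists and particularly the participants would consider changes meaningful, this study would provide first evidence of efficacy and relevance of this game-based intervention".

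The hypothesis in the Background is comparative: ten game sessions alongside rehabilitation should "improve SVMC more than standard rehabilitation alone".

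**The concern.** The baseline phase is the comparator in this design. Each child receives rehabilitation alone, then rehabilitation plus the game. An efficacy statement therefore needs a contrast between the two phases, and the ratings as described do not provide one. A child who improves at the same pace in both phases could truthfully be rated better after the intervention, and the closing sentence would count that rating in the game's favour.

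Expectation adds to the problem. The section on randomization and blinding says that participants cannot be blinded to phase, yet the closing sentence gives their opinion particular weight. The blinded evaluation described there covers the videotaped SCALE and SCUES, not the global rating.

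At stake is how the ratings would be reported. Favourable answers could be presented as support for the treatment when they could equally reflect the background programme, natural recovery or the wish to see a benefit.

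**Working it through.** The plan attaches no figure to the ratings, so there is none to reproduce. The planned 20 participants come from the primary outcome and do not enter here. The check sets the relevant statements side by side.

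**Inputs**

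- Contrast that defines efficacy (Background): game plus rehabilitation against rehabilitation alone.
- Background treatment (Discussion, paragraph on limitations): the regular programme runs in both phases, and the game is a small part of the total therapy.
- How the protocol handles concomitant therapy and spontaneous recovery (same paragraph): by comparing trends between phases, or changes relative to phase length.
- Period rated by the therapist (Discussion, final paragraph): the intervention. No rating of the baseline phase appears in that paragraph, in the outcome sections or in the Statistics section.
- Blinding (Randomization and blinding): not possible for participants. None is described for the rating therapist.
- Phase lengths (Study design): baseline 5 to 10 weekdays, intervention 10 to 13 weekdays.

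**Step 1: what one rating contains.** Write the perceived change behind the therapist's rating as

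Y_I = b × d_I + g + e_I

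Here b is the change per weekday from rehabilitation and recovery, d_I the length of the intervention phase, g the effect of the game, and e_I the effect of expectation. With Y_I alone, g cannot be identified. Setting g = 0 still gives Y_I = b × d_I + e_I, which is positive whenever b is positive and e_I is not negative.

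**Step 2: what a second rating adds.** For the baseline phase, Y_B = b × d_B + e_B. The difference is

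Y_I − Y_B = g + (e_I − e_B) + b × (d_I − d_B)

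Most or all of the background change now cancels. Two terms remain:

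- Length: d_I − d_B runs from 10 − 10 = 0 to 13 − 5 = 8 weekdays, and d_I / d_B from 10/10 = 1.0 to 13/5 = 2.6. At a constant pace of background improvement, the intervention phase would show between the same change and 2.6 times the change of the baseline phase.
- Expectation: e_I − e_B does not vanish, because raters know when the game was added.

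The five-point scale is ordinal, so this describes the perceived change behind the rating, not the scores themselves.

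**Step 3: compare with the protocol's own standard.** The Discussion names concomitant therapy and spontaneous recovery as influences and offers the phase comparison as the answer. The primary model meets that standard through the session-by-phase interaction. The clinical SVMC, cortical excitability and functional independence measures meet it through paired comparison of change in the two phases. The global rating does not, yet its closing sentence draws an efficacy conclusion.

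**The case against.** The strongest reply is that the rating was never meant as an efficacy outcome. It is introduced as an anchor for two assessments that are themselves added only before and after the intervention phase, so it covers exactly the window it needs to. No test, threshold or decision depends on it. The Statistics section defines the efficacy analysis as the mixed model. The closing sentence says that the study, not the ratings, would provide evidence, and it can be read as taking efficacy from the phase-compared results and relevance from the ratings.

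Most of this stands. A one-phase rating is adequate as an anchor, and an unblinded clinician is acceptable for that role. What does not stand is the last step. The sentence makes the ratings its only stated condition and applies it to efficacy as well as relevance.

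A reader might infer more than the document supports:

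- *That the trial's efficacy conclusion has no comparator.* It has one, in the primary model and in the paired phase comparisons. The sentence also never says that ratings alone would suffice.
- *That this is the only measure outside the phase comparison.* The two added assessments are taken only around the intervention. Follow-up is compared with measurements from before and after it, and TMS differences from before to after the intervention are correlated with SVMC change.
- *That the participant item allows only a favourable answer, or is tied to the intervention phase.* The article paraphrases the question and gives neither response options nor a reference period. What can be said is that no separate baseline-phase rating is described.
- *That the rating therapist helped choose the target.* The Intervention section says "This combination will be selected according to the participants’ individual goals and in consultation with their therapist", but it does not say that this is the therapist who later rates. Movement scientists, not the rating therapist, deliver the game.
- *That a certain number of children would be rated improved without any training effect.* The document gives no improvement rate under rehabilitation alone. Its remark that SVMC is seldom a goal of other therapies suggests that the background share may be small.

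**Conclusion.** The point holds as a fault of inference, supported by a missing comparator. The ratings as described cannot distinguish the game from background therapy, recovery or expectation, so they cannot be a basis for an efficacy claim. They remain usable as an anchor for meaningful change and as evidence of perceived relevance.

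Its reach is limited. The primary analysis and the listed secondary analyses do not use the ratings, and no sample size or error rate changes. No numerical bias is claimed. The conclusion needs only that background change or expectation may be non-zero, and the Discussion itself allows for therapy effects and recovery. It also assumes that the full protocol does not contain a baseline-phase rating that the article leaves out. Even if it did, the closing sentence would need rewording, because it refers to no comparison between phases.

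**What to change.** 1. At the transition appointment from baseline to intervention, which already takes place, ask the therapist and the participant the same global-change question, covering the baseline phase. Repeat it in the same form after the intervention.
2. Report the within-child difference between the two ratings descriptively. State beside it that the rated periods differ in length (5 to 10 versus 10 to 13 weekdays), which tends to favour the intervention phase, and that raters know the phase, so expectation is not removed.
3. Reword the closing sentence of the Discussion so that efficacy rests on the phase-compared outcomes, and favourable intervention-phase ratings support only perceived relevance and meaningful change.
4. Keep the intervention-phase rating unchanged as the anchor for the responsiveness work.

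The cost is one extra question per child and per therapist at an existing appointment, plus a change of wording. The unequal phase lengths are the small drawback. For children who have already passed the transition, a baseline-phase rating could not be recovered reliably. If the extra rating cannot be added, step 3 alone removes the unsupported claim and requires no data collection.
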